## Abstract

**Background:**

Ovarian cancer ranks 12th in cancer incidence among women in the United States and 5th among causes of cancer-related death. The typical treatment of ovarian cancer focuses on disease management, with little attention given to the survivorship needs of the patient. Qualitative work alludes to a gap in survivorship care; yet, evidence is lacking to support the delivery of survivorship care for individuals living with ovarian cancer. We developed the POSTCare survivorship platform with input from survivors of ovarian cancer and care partners as a means of delivering patient-centered survivorship care. This process is framed by the chronic care model and relevant behavioral theory.

**Objective:**

The overall goal of this study is to test processes of care that support quality of life (QOL) in survivorship. The specific aims are threefold: first, to test the efficacy of the POSTCare platform in supporting QOL, reducing depressive symptom burden, and reducing recurrence worry. In our second aim, we will examine factors that mediate the effect of the intervention. Our final aim focuses on understanding aspects of care platform design and delivery that may affect the potential for dissemination.

**Methods:**

We will enroll 120 survivors of ovarian cancer in a randomized controlled trial and collect data at 12 and 24 weeks. Each participant will be randomized to either the POSTCare platform or the standard of care process for survivorship. Our population will be derived from 3 clinics in Texas; each participant will have received some combination of treatment modalities; continued maintenance therapy is not exclusionary.

**Results:**

We will examine the impact of the POSTCare-O platform on QOL at 12 weeks after intervention as the primary end point. We will look at secondary outcomes, including depressive symptom burden, recurrence anxiety, and physical symptom burden. We will identify mediators important to the impact of the intervention to inform revisions of the intervention for subsequent studies. Data collection was initiated in November 2023 and will continue for approximately 2 years. We expect results from this study to be published in early 2026.

**Conclusions:**

This study will contribute to the body of survivorship science by testing a flexible platform for survivorship care delivery adapted for the specific survivorship needs of patients with ovarian cancer. The completion of this project will contribute to the growing body of science to guide survivorship care for persons living with cancer.

**Trial Registration:**

ClinicalTrials.gov NCT05752448; https://clinicaltrials.gov/study/NCT05752448

**International Registered Report Identifier (IRRID):**

PRR1-10.2196/48069

## Introduction

Ovarian cancer ranks twelfth in cancer incidence among women in the United States but fifth among causes of cancer-related death [1,2]. Treatment of ovarian cancer has benefited from recent scientific advances; however, the impact of novel treatments, including maintenance therapies, on life expectancy remains unclear [3]. Women with ovarian cancer typically complete their initial round of treatment with no evidence of disease but have a high risk of recurrence, with a majority of patients experiencing recurrence 18-24 months after the completion of initial platinum-based chemotherapy [4,5]. The focus becomes disease management, with an emphasis on treatment of cancer, minimization of toxicities, and optimization of quality of life (QOL). Historically, little attention has been paid to the survivorship needs of persons living with controlled cancer, advanced disease, and cancers that have high recurrence rates [6]. Qualitative work describes the unmet need for survivorship in this space of uncertainty, but there is little evidence to guide the delivery of survivorship care for persons living with cancer as a chronic condition.

Cancer health services science incorporated cancer survivorship as a target for care improvement following the 2006 publication of the seminal work “*From Cancer Patient to Cancer Survivor: Lost in Transition*” [7]. This foundational work summarized the challenges associated with cancer survivorship care, including the absence of systematic strategies for care provision, coordination of care across settings, unmet symptom management and psychosocial needs, and an unclear locus of responsibility for care. Subsequent years have seen dramatic increases in cancer survivorship science publications and the development of interventions and programs to meet the needs of cancer survivors. Science, however, has disproportionately focused on breast cancer and other “curable” cancers, and gaps in science and care for persons living with serious or incurable cancer remain to be addressed.

Ovarian cancer is a model of those cancers not typically encompassed in survivorship science and care. Over 19,000 women in the United States will receive a new diagnosis of ovarian cancer this year. For most of them, the point of diagnosis is the beginning of several years of living with cancer, treatment, and uncertainty. Most of these women will be diagnosed with advanced disease; 4 out of 5 patients have regional or advanced disease at the time of diagnosis. This contributes to the unfortunate outcomes associated with ovarian cancer, and 5-year survival rates remain below 50% despite improvements over the past 10 years. Women with ovarian cancer typically undergo treatments including surgery, chemotherapy, sometimes radiation therapy, and increasingly maintenance therapy with targeted therapies [8]. Survivorship care needs for women with ovarian cancer are unique, and frequently, their gynecologic oncology treatment program will also serve as the site of much of their cancer-focused survivorship care [9,10]. Most patients experience residual physical and psychological symptoms posttreatment [11]. Recurrence anxiety, psychosocial needs, sexual functioning, depressive symptoms, and uncertainty related to the care plan moving forward are all reported as sources of impaired well-being among ovarian cancer survivors [12-16]. Women with ovarian cancer being treated in safety net systems are more likely to have poor QOL and less likely to comply with follow-up visits, etc, making it more imperative to develop systems and processes to facilitate their survivorship transition.

Few studies have examined the impact of survivorship care plans (SCPs) for survivors of ovarian cancer on their QOL. The Registration System Oncological Gynecology trial was a pragmatic cluster randomized trial in which 12 hospitals were randomized to deliver computer-generated SCPs or usual care. The SCP was based on a Dutch translation of the Institute of Medicine format [7]. A total of 174 patients with ovarian cancer enrolled in the trial, of whom 61 received care at an SCP hospital and 113 received care at a usual care hospital. The primary analysis outcomes included satisfaction with care, illness perception, and health care use. There were no overall effects of SCP delivery on any of the scales of satisfaction with care; at 12 months of intention to treat (ITT) analysis, patients in the SCP arm rated the interpersonal skills of nurses lower than patients in the usual care arm. Patients in the SCP arm experienced more symptoms, were more concerned about their illness, and were more emotionally affected than patients in the usual care arm [17]. Further analyses showed increases in health care use among women with anxiety symptoms and those who received radiotherapy [18,19]. Investigators found that patients with ovarian cancer who had lower trust that the treatment would cure their disease due to the SCP reported worse emotional functioning 6 months after treatment [20]. Taken in total, the Registration System Oncological Gynecology trial underscores that for women with ovarian cancer, a templated SCP that emphasizes the frightening long-term outcomes of this disease may impair outcomes. In response to this study and the concerns of our patients, we engaged patients with ovarian cancer and providers to provide input on the development of POSTCare-O. Their input resulted in a goal related to living well with a serious illness and the inclusion of specific strategies to cope with recurrence anxiety.

We developed the POSTCare survivorship transition platform to deliver a patient-centered and Institute of Medicine (now National Academy of Medicine)–adherent SCP in breast cancer. Women with ovarian cancer experience a significant symptom burden resulting from depression and anxiety [12]. This burden is substantially higher compared with that observed in healthy populations of women and is a phenomenon that persists years into survivorship [15]. The impact of the POSTCare survivorship transition platform on reducing depressive symptom burden has been observed among survivors of breast cancer [21]. However, it remains unknown what effect the adapted intervention may have on patients with ovarian cancer. For this population, the intervention has been modified to target coaching toward the concept of “living well with a serious illness” and symptom self-management. Participants identifying a goal related to recurrence anxiety will receive a brief cognitive intervention based on acceptance and commitment therapy [22]. Strategies to address these issues in survivors of ovarian cancer are currently lacking, and this study may identify potential pathways for improved psychosocial well-being.

The POSTCare survivorship care platform is framed by the chronic care model [23,24] and is also informed by the wealth of literature on care setting transition support [25-27] and patient informants (Figure 1) [28]. Designed to be delivered through telehealth or in-person, POSTCare is best understood as a health services delivery platform that coaches the survivor to engage as an activated agent in her own survivorship care. Recommendations are anchored in existing evidence-based approaches that have historically not found avenues for effective dissemination. The POSTCare platform explicitly maps onto the chronic care model essential elements, including self-management coaching and support directed at both symptoms and wellbeing for survivors. The engagement of community resources occurs with services such as exercise or mental health care to support patients’ goals. Delivery system design includes the platform’s “plug and play” approach to evidence-based behavioral change support that allows the nature of survivorship support to adjust to patients’ needs and goals. Decision support for providers delivering care is built into the platform in a “tool kit” of evidence-based behavioral interventions to support patients’ goals [29]. We hypothesize that POSTCare will increase the effective use of evidence-based care and improve outcomes for patients.

**Figure 1 figure1:**
[figure not shown]
Alignment of POSTCare elements with the chronic care model. Developed by The ACT Center, formerly known as the MacColl Center for Health Care Innovation, reprinted with permission from ACP-ASIM Journals and Book.

In POSTCare-O, the POSTCare platform is adapted to meet the needs of survivors of ovarian cancer. We worked with members of the CanSurvive GYN Cancer Support Group in Birmingham, Alabama, and gynecologic oncologists to identify survivorship priorities and needs. Patients with ovarian cancer and their caregivers were clear that they wanted to focus on living well during the survivorship transition, and clinicians felt that concerns that may be important for other cancer types, such as transition to primary care, might be of lesser priority in the context of ovarian cancer. They helped us understand that the essential “work” of cancer survivorship in ovarian cancer is the work of living well despite serious illness and the specter of mortality. Using the palliative dual framework, a technique used to assist patients in the task of living well despite serious illness [30,31], and a brief acceptance and commitment therapy intervention [22], we have incorporated a goal focused on living well with a serious illness that was not a component of the breast cancer POSTCare platform.

The overarching goal of this study is to test processes of care that support outcomes, including QOL, in survivorship. We will use QOL as a primary outcome, but we will also look at factors such as recurrence worry, depressive symptom burden, and survivorship efficacy that may also be influenced by improved care processes. The specific aims of this study are to conduct a randomized controlled trial (RCT) enrolling 120 women with advanced ovarian cancer. We will test the efficacy of the POSTCare platform in supporting QOL, reducing depressive symptom burden, and reducing recurrence worry. In our second aim, we will examine factors associated with the impact of the intervention. Our final aim focuses on understanding aspects of care platform design and delivery that are likely to affect the potential for dissemination. We will use both qualitative and quantitative methods to assess patient experience, provider experience, and pragmatic aspects of clinical implementation, with the goal of redesigning the implementation for greater dissemination potential.

## Methods

### Study Design

We will conduct a 2-arm RCT to evaluate the impact of a telehealth-delivered survivorship transition care platform. Survivors of ovarian cancer (N=120) will be randomly allocated to receive survivorship care either using the POSTCare Platform or standard of care. Study design and reporting will be in accordance with the CONSORT (Consolidated Standards of Reporting Trials) checklist. We will use quantitative and qualitative methodologies in a concurrent triangulation mixed methods design using qualitative data to augment our interpretation of quantitative data. Outcomes will be collected at baseline, 12 weeks, and 24 weeks, with the primary outcome being a QOL assessment at 12 weeks after the survivorship transition (Figures 2 and 3).

**Figure 2 figure2:**
[figure not shown]
POSTCare-O randomized clinical trial flow demonstrating enrollment, randomization, and data collection time points.

**Figure 3 figure3:**
[figure not shown]
Mixed methods framework demonstrating data sources and integration schema.

### Sample Size

We will enroll 120 women completing primary treatment for stage 2-4 ovarian cancer from 3 urban gynecologic oncology clinics located in the US state of Texas. Participants will have received some combination of surgery, chemotherapy, radiation therapy, and biologics. Continued maintenance therapy is not an exclusion factor. The disease-stage sample frame was developed with input from our gynecologic oncology collaborators based on treatment exposures and the similarity of survivorship challenges. Aim 1 proposes to implement a RCT devised to compare QOL measures among patients with ovarian cancer randomized to receive usual care versus the POSTCare survivorship care transition program. The Functional Assessment of Cancer Therapy-Ovarian (FACT-O) QOL survey will be collected at baseline as well as 12 and 24 weeks after the initial course of adjuvant chemotherapy. The primary end point will be the 12-week survey. The sample size of 120 patients provides at least 80% power to detect a 7% increase in the mean FACT-O score for women randomized to the POSTCare survivorship care intervention. This is sufficient to ascertain a minimally important difference of 8 points [32].

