### Recruitment and Setting

We will recruit participants from gynecologic oncology practices at 3 clinic settings in Texas: 1 safety net practice located in Dallas, 1 safety net practice located in Houston, and 1 faculty group practice located in Houston. Cumulatively, the sites serve approximately 140 eligible patients per year and ensure a diverse population of 120 participants can be recruited during the 24-month recruitment period. A total of 60 participants will be randomly assigned to the intervention group and receive care using the POSTCare process, and another 60 will be randomly assigned to the control group. To be included, patients must (1) be diagnosed with ovarian cancer at the age of 18 years or older; (2) be within 3 months of completing initial treatment for stage 2-4 ovarian cancer. Treatment may include surgery, chemotherapy, radiation therapy, immunotherapy, or other biologics. Participants may be on maintenance therapy; and (3) be able to provide consent in English or Spanish. Patients who are enrolled in hospice care directly following the treatment conclusion will not be eligible for the study. It is anticipated that this study sample will reflect the ethnic and racial diversity of our clinical settings.

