### Recruitment Procedures

Study research coordinators will have access to the electronic medical record at each site. They will collaborate with clinical personnel to identify patients who will be completing initial therapy. Coordinators will work to identify patients in treatment at least 8 weeks before the completion of therapy. They will identify an upcoming clinical appointment, either in clinic or infusion, where the team will approach patients to provide information about the study, answer questions they may have, and obtain informed consent. Enrolled participants will be asked to complete a web-based, self-administered survey using a smart device to collect baseline measurements before randomization.

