Booster survivorship navigation telephone contacts occur at 4 weeks and 8 weeks after baseline. The survivorship coaches will review health goals, including living well, adjust goals as needed, discuss progress, identify barriers, and brainstorm about strategies to overcome barriers. The survivorship coaching intervention is delivered through telehealth by the nurse survivorship navigation coach. For participants who do not have a smart device, the intervention can be delivered through a smart device provided by the study in a clinic setting.

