Other measures used as secondary outcomes and potential predictors were selected with a priority on acceptable psychometric performance in similar populations and acceptable performance in one of our previous studies.

“Aim 1” proposes to implement a RCT devised to compare QOL measures among patients with ovarian cancer randomized to receive usual care versus the POSTCare survivorship care transition program. Outcome measures, including the FACT-O QOL survey, the FCR-7 survey, and the PHQ-9, will be collected at baseline as well as 12 and 24 weeks after the initial course of adjuvant chemotherapy. The primary end point will consist of the 12-week FACT-O survey. The sample size of 120 patients provides at least 80% power to detect a 7% increase in the mean FACT-O score for women randomized to the POSTCare survivorship care intervention. This is sufficient to ascertain a minimally important difference of 8 points. Secondary outcomes (Table 1) will also be assessed at 12 and 24 weeks. Baseline descriptive statistics will be presented by site. Longitudinal analysis of the FACT-O QOL scores will use a mixed effects linear model with a restricted maximum likelihood estimation method, and an unstructured covariance matrix will be used to estimate trends. An interaction between intervention and time will be estimated to explore the effectiveness of POSTCare for time-varying trends [49]. Though the mixed effect model can accommodate some degree of missing data under the ignorability assumption, we also plan to use multiple imputations using the random forest method [50,51] to accommodate missing data (if greater than 10% of survey items), which will be assumed to be missing at random. In the event of a sign of a violation of that assumption, a pattern mixture model will be used to mitigate the effect of informative missingness. Secondary analyses will evaluate relationships between baseline and 12-week FACT-O scores and clinical end points progression-free survival (PFS) and overall survival (OS). Cox proportional hazard models will be used to estimate the relative risk of PFS and death per increase in FACT-O [52]. Ties in failure times will be handled with the approximate likelihood of Efron. PFS and OS will be measured from the date of randomization. PFS is defined as the minimum amount of time until clinical progression, death, or the date of last contact. OS is the duration from randomization to death or to the date of last contact (right-censoring). As is customary, secondary analyses are not powered but may help generate additional evidence that needs to be tested in the future by a properly powered study.

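### The 12-week primary FACT-O survey has three stated time origins that conflict, and the chemotherapy-based one gives unequal intervention exposure at week 12

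*Protocol article*

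**What the plan says.** All references are to the protocol article.

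**Survey timing.** Three origins are stated for the 12-week survey:
- Abstract, Results: the effect is examined "on QOL at 12 weeks after intervention as the primary end point".
- Study Design: "with the primary outcome being a QOL assessment at 12 weeks after the survivorship transition".
- Sample Size: the FACT-O "will be collected at baseline as well as 12 and 24 weeks after the initial course of adjuvant chemotherapy". Outcome Measures repeats this origin for the FACT-O, FCR-7 and PHQ-9: "12 and 24 weeks after the initial course of adjuvant chemotherapy".

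Study Design also lists the visits with no origin: "Outcomes will be collected at baseline, 12 weeks, and 24 weeks".

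**Intervention timing.** Patient-Centered Design uses another clock: "Booster survivorship navigation telephone contacts occur at 4 weeks and 8 weeks after baseline". The lag from baseline to the initial visit is not given.

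**Entry.** Recruitment and Setting requires a woman to "be within 3 months of completing initial treatment for stage 2-4 ovarian cancer", and lists chemotherapy among treatments that she may have had, not as a requirement. Recruitment Procedures starts earlier: "Coordinators will work to identify patients in treatment at least 8 weeks before the completion of therapy". The baseline survey precedes randomisation.

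Randomisation is named as a time origin only for progression-free and overall survival (Outcome Measures).

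**The concern.** A primary end point needs one clock. Here the sections that describe data collection in most detail use an origin, chemotherapy, that is tied neither to randomisation nor to the intervention. Women may enter anywhere from during therapy to 3 months after it, so a fixed interval from chemotherapy is not a fixed interval from baseline. The planned mixed model with an unstructured covariance matrix treats weeks 12 and 24 as common occasions. If one woman's week 12 falls after both boosters and another's before either, the treatment contrast at that occasion averages over different amounts of intervention. The 24-week survey, which supplies the Aim 2 end point, and the mediators collected at 12 and 24 weeks carry the same ambiguity.

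**Working it through.** The plan gives no figure for survey timing relative to baseline, so there is none to reproduce. The check is date arithmetic.

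**Inputs.**
- Survey at 12 weeks after chemotherapy, read as after the end of the course (Sample Size, Outcome Measures).
- Boosters at weeks 4 and 8 after baseline (Patient-Centered Design).
- Entry up to 3 months, about 13 weeks, after completing initial treatment (Recruitment and Setting).
- Identification at least 8 weeks before therapy ends (Recruitment Procedures).

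**Formula.** Let T be the weeks from the end of chemotherapy to baseline, negative if baseline is taken during therapy. The survey then falls 12 − T weeks after baseline.

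| T (weeks) | Survey, weeks after baseline | Position |
|---|---|---|
| −8 | 20 | 12 weeks after the second booster |
| 0 | 12 | 4 weeks after the second booster |
| 4 | 8 | at the second booster |
| 8 | 4 | at the first booster |
| 12 | 0 | at baseline |
| 13 | −1 | before baseline |

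The thresholds follow directly: before the second booster if 12 − T < 8, so T > 4; before the first if 12 − T < 4, so T > 8; before baseline if T > 12. They need no assumption about how T is distributed.

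**Illustrative shares.** The distribution of T is not given. Two assumptions show a range:

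| Survey falls before | T uniform on 0 to 13 | T uniform on −8 to 13 |
|---|---|---|
| second booster (T > 4) | 9/13 = 69% | 9/21 = 43% |
| first booster (T > 8) | 5/13 = 38% | 5/21 = 24% |
| baseline (T > 12) | 1/13 = 8% | 1/21 = 5% |

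**Initial visit.** If this visit takes place at baseline, the share surveyed before it is the last row, 8% or 5%. With an assumed lag of 2 weeks the condition becomes T > 10, giving 3/13 = 23% or 3/21 = 14%. With an assumed lag of 4 weeks it becomes T > 8, giving 38% or 24%.

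**Cases outside the formula.** A woman treated without chemotherapy has no T and so no survey date. If other initial treatment follows chemotherapy, T can exceed 13 weeks, because the entry window runs from the end of treatment, not of chemotherapy.

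**Comparison with a baseline clock.** Timed from baseline, or from randomisation just after it, the survey falls at about week 12 for every woman, 4 weeks after the second booster.

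**The case against.** The best defence is that the chemotherapy phrase is loose wording. A follow-up survey before baseline cannot be carried out in practice, the listed schedule of baseline, 12 and 24 weeks suggests a clock from baseline, and boosters at weeks 4 and 8 fit a survey at week 12. Figure 2 is described as showing the data collection time points and is not available here; it may show the schedule in use. This may well be how surveys are sent. It does not remove the conflict: the phrase appears in two sections, and no sentence times the survey from baseline or randomisation.

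Several stronger readings are tempting, and the documents do not support them.
- *Four survey origins.* Only three are explicit. Baseline times the boosters, not the survey, and the intervention and the survivorship transition may be one visit, since the platform opens with a transition visit.
- *Many women surveyed before the intervention is delivered.* This holds only if delivery means that both boosters are complete. If the initial visit is at or near baseline, women have already had the main coaching session. Larger shares before that visit need an assumed lag.
- *Entry spread evenly over the 3 months.* Three months is the outer limit. Recruitment aims to find women during therapy, and if entry clusters at its end, few or none would be surveyed before the initial visit.
- *A week-20 survey under the Abstract's wording.* This counts from the last booster (8 + 12 = 20), which no section does.
- *Bias between arms.* Both arms have a survivorship visit, no section gives them different timing, and a chemotherapy clock does not depend on arm. Randomisation balances time since treatment in expectation.

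**Conclusion.** The point holds as an internal contradiction in the definition of the primary end point: three stated origins, of which at least two are plainly different events. The chemotherapy origin misfires as written. With entry allowed to about 13 weeks, it can place the week-12 survey before either booster and, for the latest entrants, before baseline. For women enrolled during therapy it falls later than 12 weeks after baseline, and for women without chemotherapy it is undefined.

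The thresholds (T above 4, 8 and 12 weeks) follow from the stated text. The shares, 69%, 38% and 8% or 43%, 24% and 5%, rest on assumed uniform entry and show only what is possible. The consequence is variable exposure at the primary time point, with a diluted effect and added variance. The documents do not allow the dilution to be put in FACT-O points.

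**What to change.** Time the 12- and 24-week surveys from randomisation, with the baseline survey just before it and the same visit window in both arms. Bring the Abstract (Results), Study Design, Sample Size and Outcome Measures into line with that wording. Weeks since the end of treatment at randomisation may enter the model as a baseline covariate; they should not serve as the clock.

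The text change and the survey trigger in the data system need no extra patients or visits. Data collection began in November 2023, however, so the cost may go beyond wording. The sponsor should confirm which date has triggered surveys so far and report the actual survey timing relative to randomisation. If randomisation or baseline has been used throughout, only the text changes. If chemotherapy dates have been used, surveys already collected will vary in timing, and the analysis has to account for that.
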